### Exploratory objectives

To analyze whether the change in pain intensity from baseline to the last week of lacosamide and placebo treatment depends on preserved thermal sensation (QST), gain of sensation (QST), pain characteristics as determined by the NPSI, or evoked pain ratings in the bedside sensory testingIf there is no phenotype difference, we will compare the primary and secondary outcomes in the total populationTo analyze whether there is a correlation between the percentage change in pain score from the baseline week to the last week of treatment and the effect of conditioned pain modulation (CPM) [6]To analyze predictors of the placebo response (CPM, patient expectation, age, gender, anxiety and depression scores at first examination, pain duration, baseline pain variability, and adverse events)

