### Statistics

With a minimally relevant between-phenotype group difference in total pain reduction of 1.25 NRS points, a standard deviation of 1.6 within phenotype groups [5], 80% power, and a 5% risk of type I error, the sample size estimate is 27 + 27 patients for the primary objective. With a minimally relevant treatment versus placebo difference in total pain reduction of 1.5 NRS points, 80% power, and a 5% risk of type I error, the sample size estimate is 30 + 15 patients using a treatment:placebo ratio of 2:1 for the supportive objective. With an expected dropout rate of 1/6 (data available for intention-to-treat (ITT) analysis), the recruitment stops when 54 patients in each phenotype group have been randomized to lacosamide and placebo in a 2:1 ratio. Thus, we expect to randomize 108 patients. For the explorative outcome in case there is no phenotype difference, 72 patients randomized to lacosamide and 36 patients randomized to placebo in the total population in an ITT population will give > 90% power to find a minimally relevant treatment versus placebo difference in total pain reduction of 1.25 NRS points and 85% power to find a minimally relevant treatment versus placebo difference in total pain reduction of 1.0 NRS points.

Statistical analysis of the primary outcome will be performed by *t* test and of the secondary outcomes by the Mann–Whitney *U* test. Nondichotomous tertiary outcomes will be performed by *t* test or Mann–Whitney *U* test, where applicable. Since we do not expect differences in baseline between the two phenotypes [5], a major impact of baseline pain intensity on the outcome, or a center effect, we do not plan to include these as covariates in the analyses.

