For the primary outcome, the delta values from the average pain intensity in the baseline week to the last treatment week (last 7 days) will be used. Response rates and other dichotomous data are analyzed using Fisher’s exact test. For the primary (and supportive) objective, we are interested in the mechanistic aspects and in understanding whether the sensory phenotype “irritable nociceptor” is a prognostic biomarker for a sodium channel blocker in therapeutic doses. Therefore, the primary analysis for the primary objective is the PP population. Missing data will not be replaced. The PP population comprises those patients who complete at least 2 weeks on stable medication with at least 100 mg bid. Thus, if patients who fulfil the PP definition stop the treatment before the 12th week, the last seven pain scores on stable medication will be used for the primary analysis, and they will be invited for an additional visit identical to visit 3. All patients who have taken at least one study capsule will be encouraged to stay in the study, complete the diary, and come for a visit after 12 weeks.

As a secondary analysis, the ITT population will be used. The ITT analysis will also be used for the explorative outcome in the whole population if there is no phenotype difference. Given a substantial dose-dependent withdrawal rate due to adverse events, the EMA suggests a conservative responder analysis and that noncompleters are defined as nonresponders [19]. Therefore, the baseline observation carried forward (BOCF) in the ITT population (all patients randomized) will be the primary imputation method, and the last observation carried forward (LOCF) will be done as a secondary imputation method. Patients will be asked to complete the pain diaries despite their withdrawal from trial medication to minimize the need for imputation.

Significance is considered at the 5% level. If there are changes to the original statistical plan, the type of change and the date of change will be documented, and the document will be signed by the sponsor.

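### The whole-population lacosamide–placebo comparison is made conditional on no phenotype difference, so a non-randomised contrast decides whether the plan provides a pooled randomised estimate

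*Protocol article*

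**What the plan says.** The condition appears three times in the Protocol article.

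- Exploratory objectives: if "there is no phenotype difference, we will compare the primary and secondary outcomes in the total" population.
- Statistics, power statement: "For the explorative outcome in case there is no phenotype difference, 72 patients randomized to lacosamide and 36 patients randomized to placebo" are said to give more than 90% power at 1.25 NRS points and 85% at 1.0.
- Statistics, on the analysis populations: "The ITT analysis will also be used for the explorative outcome in the whole population if there is no phenotype difference".

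The article does not define the absence of a phenotype difference by an equivalence margin, a confidence-interval criterion or an interaction test. The one decision rule it gives is: "Significance is considered at the 5% level".

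Under Objective, the primary comparison sets the pain change in lacosamide patients with the irritable nociceptor phenotype against that in lacosamide patients without it, in the per-protocol population. The supportive objective compares lacosamide with placebo in each phenotype and carries no such condition. ITT is the secondary analysis population. No whole-population comparison is described for the case where a phenotype difference is found.

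**The concern.** Whether the pooled drug–placebo comparison is planned depends on the result of another test on the same patients, and that test is poorly suited to the job in three ways.

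- A p-value above 0.05 is not evidence that two groups respond alike. At this sample size it is compatible with differences that the protocol itself calls relevant.
- The test looks at lacosamide patients only. Phenotype is not randomised, so a difference can be prognostic (one phenotype improves more on anything) rather than a difference in drug effect.
- The test is per-protocol, yet it decides whether an ITT comparison of all randomised patients is made.

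The Background calls the effect of lacosamide in neuropathic pain inconclusive, and the Abstract hopes to inform its usefulness. An overall randomised estimate is therefore of interest whichever way the phenotype test falls. Under the written rule it can go unreported. In the other direction, a pooled estimate may be read as applying equally to both phenotypes when the data have not shown that.

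**Working it through.** **Inputs (Statistics section).** Phenotype difference: "With a minimally relevant between-phenotype group difference in total pain reduction of 1.25 NRS points". Spread: "a standard deviation of 1.6 within phenotype groups". Primary size: "80% power, and a 5% risk of type I error, the sample size estimate is 27 + 27 patients for the primary objective". Supportive comparison: "With a minimally relevant treatment versus placebo difference in total pain reduction of 1.5 NRS points", with 30 + 15 patients. Expected dropout is 1/6, and 72 + 36 are randomised in total. Assumed here: two-sided tests, the same SD of 1.6 throughout, and equal placebo response in the two phenotypes.

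**Formula.** λ = δ / [σ√(1/n₁ + 1/n₂)]. Power = P(|T| > t₀.₉₇₅), where T is noncentral t with n₁ + n₂ − 2 degrees of freedom.

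**1. The plan's own figures reproduce.**
- Primary, 27+27, δ = 1.25: SE = 1.6√(2/27) = 0.435; λ = 2.87; power 80.4%.
- Whole population, 72+36: SE = 1.6√(1/72 + 1/36) = 0.327. At 1.25, λ = 3.83 and power is 96.7% (stated: above 90%). At 1.0, λ = 3.06 and power is 85.9% (stated: 85%).

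No stated figure is wrong. The fault lies in the conditional rule.

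**2. What a non-significant primary test can exclude.** The 95% CI half-width with 27+27 is 2.007 × 0.435 = 0.87 points. Any non-significant observed difference above 1.25 − 0.87 = 0.38 therefore has an interval that contains 1.25.

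**3. How often the test is non-significant.**

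| True phenotype difference | 27+27 | 30+30 |
|---|---|---|
| 0 | 95% | 95% |
| 0.5 | 80% | 78% |
| 0.75 | 61% | 57% |
| 1.0 | 38% | 34% |
| 1.25 | 20% | 15.5% |

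The first row also shows that 5% of trials lose the pooled comparison by chance when there is no difference at all.

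**4. What the test measures.** Let e₁ and e₀ be the drug effects over placebo in the two phenotypes, and p₁ and p₀ the placebo responses. The difference among lacosamide patients is (e₁ − e₀) + (p₁ − p₀). The interaction is e₁ − e₀. They are equal only if p₁ = p₀, which the authors expect but which the primary test does not examine.

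**5. What is lost.** Simulated trials with 30+30 lacosamide and 15+15 placebo (60+30 pooled); repeat runs move the figures by about one percentage point at most. The effect pairs are illustrative assumptions.

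| Effects in the two phenotypes | Primary test significant (no pooled analysis planned) | Pooled power | Pooled test both run and significant | Power in the more responsive phenotype, 30+15 |
|---|---|---|---|---|
| 1.0 / 1.0 | 5% | 79% | 75% | 49% |
| 1.5 / 0.75 | 43% | 86% | 49% | 83% |
| 1.5 / 0.5 | 66% | 77% | 26% | 83% |
| 1.5 / 0.25 | 85% | 64% | 10% | 83% |

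The 60+30 is what remains of 72+36 after 1/6 dropout. The planned ITT set is all 72+36 with imputation, so these pooled powers are approximate.

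**The case against.** Several points on the other side stand.

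- *Randomised evidence is not abandoned.* Lacosamide is compared with placebo in each phenotype whatever the primary result, and ITT is a secondary analysis. Together these cover every randomised patient. With 54 recruited per phenotype, a reader could roughly average the two effects. It would be wrong to infer that the trial could end with no randomised efficacy evidence.
- *The pooled comparison is not always the best powered.* It is when effects are similar: at 1.0 in both phenotypes, 79% (60+30) against 49% (30+15). If the effects are 1.5 and 0.25, the pooled test has about 64% and the more responsive phenotype alone 83%. Even at 1.5 and 0.75 that phenotype's own test has 83%. A reader might infer that the rule discards the strongest comparison; that holds only for similar effects.
- *The protocol does not say that non-significance proves equality.* The trigger is not defined in this condensed article, and its exact form may be in an SAP that is not shown. Reading it as p > 0.05 is an inference from the single rule stated.
- *Giving the phenotype-specific effects priority is defensible when they differ,* since the pooled mean then depends on a recruitment quota.
- *The weak power for interaction is disclosed* in the Discussion, and the placebo arm is there to support a predictive reading.

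These points lower the weight of the concern but do not remove it. The condition itself is stated three times and is not a detail left open. Calling an analysis exploratory does not justify making its existence depend on the data, and two comparisons of 30+15 do not replace a reported overall estimate with its interval.

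**Conclusion.** The point holds in a limited form. The plan ties a pooled, randomised ITT comparison to a per-protocol, lacosamide-only contrast that can neither establish the absence of a phenotype difference nor measure a difference in drug effect. Where that contrast is significant, no pooled estimate is planned.

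The size depends on the unknown effects. It is 5% of trials if the phenotypes truly do not differ, and about 43% in the illustrative case of 1.5 and 0.75. The figures rest on SD 1.6, two-sided 5% tests, equal placebo response and the reading of the trigger as a non-significant primary test. The loss is partial and the analysis is exploratory. No primary conclusion or sample-size figure is affected. The change should be made, but the trial does not stand or fall on it.

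**What to change.** Delete the condition in the Exploratory objectives and in both places in Statistics. State instead that the exploratory whole-population ITT lacosamide–placebo difference will always be reported with its confidence interval, from a model that includes phenotype (the stratification factor). Present it beside the two phenotype-specific effects and the treatment-by-phenotype difference with its interval.

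The decision not to adjust for baseline pain or centre is a separate matter and need not be reopened for this change.

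The cost is wording and one more exploratory analysis. No patients or data are added and, as the analysis stays exploratory, no type I error is spent. One caution belongs in the text: if the effects differ, the pooled mean reflects the 54 + 54 recruitment quota and should be read only beside the phenotype-specific effects.

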### Safety

Patients will record any adverse events in the pain diary and will be interviewed at each telephone call and study visit with open questions. The type of event, times of onset and termination, severity, and relationship with the treatment drug will be recorded.

### Publication

Regardless of the outcome, the results (including positive, negative, and inconclusive results) of the trial will be published in a recognized international journal. ICMJE guidelines for authorship will be followed.

## Discussion

The main aim of this study is to assess the concept of stratification based on pain phenotyping in neuropathic pain. We aim to assess whether we can reproduce results from a previous study showing a better effect of the sodium channel blocker oxarbazepine in patients with neuropathic pain and the so-called irritable nociceptor phenotype [5]. Lacosamide is a sodium channel blocker with a different profile enhancing the slow-inactivation of voltage-dependent sodium channels [8]. The strength of the study is that the primary purpose is to compare the effect in two groups of patients with different sensory pain phenotypes and thus possible different underlying pain mechanisms and blinding of persons involved in the study to the pain phenotype. There are several limitations. An unrealistically high number of patients would be required to power the study to show a difference in the drug–placebo differential between the two groups of patients, so the study will need to rely on supportive evidence. A thorough analysis of previous studies would have been advantageous to assess whether the best statistical plan should be a regression analysis including, for example, baseline pain intensity, center, and escape medication. There is a possibility of discontinuation due to lacosamide’s potential side effects and a risk of unblinding due to side effects. In addition, we do not know the strength and reproducibility of the phenotype classification as only one sensory testing will be performed, and the classification into IN and NIN can be considered an arbitrary dichotomy of continuous measurements [20].

## Trial status

At the time of first submission, the trial had not enrolled any patients. Recruitment started February 2019 and is expected to continue until the middle of 2021.

## Data Availability

Not applicable.

## Abbreviations

bid: *bis in die* (twice daily)
CPM: Conditioned pain modulation
CRF: Case report form
IN: Irritable nociceptor
ITT: Intention to treat
NIN: Non-irritable nociceptor
NPSI: Neuropathic Pain Symptom Inventory
NRS: Numeric rating scale
PGIC: Patient Global Impression of Change
PROMIS: Patient Reported Outcome Measurement Information System
QST: Quantitative sensory testing
RCT: Randomized controlled trial
REDCap: Research electronic data capture
